## Abstract

**Background:**

Obese women have fewer oocytes retrieved, an increased cancelation rate, a higher miscarriage rate, and a lower live birth rate after assisted reproductive technology (ART) treatment compared with women with normal weight. Weight loss before ART treatment can significantly improve pregnancy rates and/or live births. An orlistat plus diet intervention could promote weight loss, but there is no evidence from randomized clinical trials evaluating the effect of orlistat preconceptional treatment on pregnancy outcome in overweight and obese women.

**Methods/design:**

We are conducting a multicenter, randomized placebo-controlled, double-blind clinical trial in overweight and obese women aged 20–40 years undergoing in-vitro fertilization and embryo transfer (IVF-ET) with or without intracytoplasmic sperm injection, to evaluate whether orlistat treatment for 1–3 months before IVF-ET can improve the live birth rate. The primary outcome is live birth.

**Discussion:**

The results of this study will provide evidence for the effect of preconceptional orlistat treatment on IVF outcome in overweight/obese women.

**Trial registration:**

Chinese Clinical Trial Registry, ChiCTR-IPR-17011629. Registered on 11 June 2017.

**Electronic supplementary material:**

The online version of this article (10.1186/s13063-018-2780-7) contains supplementary material, which is available to authorized users.

## Background

The prevalence of obesity is increasing worldwide, and it causes not only an increased risk of metabolic syndrome, type 2 diabetes, and cardiovascular disease, but also a decline in fertility and an increased risk of infertility [1]. Obese women have a higher dose of gonadotrophin, more days of stimulation, fewer oocytes [2, 3], an increased cancelation rate, a higher miscarriage rate [4], and a lower live birth rate [5, 6] compared with women with normal weight. According to a systematic review by Maheshwari et al. [7], women with BMI ≥ 25 kg/m^2^ have a lower chance of pregnancy and an increased miscarriage rate following IVF. Another meta-analysis showed similar results that women with BMI ≥ 25 kg/m^2^ had significantly lower live birth rates compared to those with BMI < 25 kg/m^2^ following IVF/ICSI treatment [8]. The risk for preeclampsia and gestational diabetes was doubled in obese pregnant women [9], and maternal obesity was associated with an increased risk of many structural anomalies [10, 11]. Short-term weight loss was associated with higher metaphase II (MII) oocyte yield, but unrelated to clinical pregnancy or live birth rates [12]. Another study reported that a “meaningful” weight loss of 10% could significantly improve live birth rates (71% vs 37%) [13]. A systematic review showed that women with weight loss before ART treatment had significantly improved pregnancy rates and/or live births [14].

A high-caloric diet is the main cause of obesity, and a higher fat intake is associated with dyslipidemia and insulin resistance. The common strategy to lose weight includes modification of unhealthy dietary habits, more physical activity, pharmacological management, and bariatric surgery. But poor patient compliance with lifestyle modification is known because it needs a long time to take effect. Therefore, it is reasonable to focus on the consumption of fat to lose weight.

Orlistat prevents the absorption of triglyceride from the human diet by irreversibly combining with gastric and pancreatic lipase, and it is reported that an orlistat plus diet intervention could decrease weight, cholesterol, and insulin levels [15, 16]. But there is no report about the effect of orlistat before ART treatment on pregnancy outcome in overweight and obese women.

## Methods/design

### Design and setting

This study is a multicenter, randomized placebo-controlled, double-blind clinical trial to evaluate whether orlistat treatment for 1–3 months before IVF-ET can improve the live birth rate. Patients are recruited from 19 hospitals in China. In this study, overweight is defined as BMI ≥ 25 kg/m^2^ and obesity as BMI ≥ 28 kg/m^2^ according to Chinese criteria.

### Inclusion criteria

The inclusion criteria are as follows:Women aged ≥ 20 and ≤ 40 years.Women with BMI ≥ 25 kg/m^2^.Women who are undergoing IVF or intracytoplasmic sperm injection (ICSI).

### Exclusion criteria

The exclusion criteria are as follows:Women who had no clinical pregnancy after three or more cycles of IVF/ICSI.Women who have been diagnosed with congenital or acquired uterine abnormalities by ultrasound or with severe intrauterine adhesion by hysteroscope.Women with abnormal liver or renal function.Women with an allergy to orlistat.Women with a diagnosis of malabsorption syndrome or cholestasis.Women with organic obesity; for example, hypothyroidism.

### Sample size

Based on the retrospective data from our IVF clinic, the live birth rate of obese or overweight women is about 35%. It is assumed that an improvement of 10% in the live birth rate will be clinically significant. We aim to test a difference of 10% in the live birth rate between treatment groups (45% in the orlistat group) at a significance level of 0.05 with a statistical power of 80%. The minimal sample size calculated is 752, and 836 participants will be enrolled in consideration of a dropout rate of 10%.

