### Outcome and outcome assessments

The primary outcome is live birth after first fresh embryo transfer. The secondary outcomes include changes of body weight, moderate and severe ovarian hyperstimulation syndrome (OHSS), dose of gonadotrophin during ovarian stimulation, numbers of oocytes, embryos of high quality, conception, clinical pregnancy, ongoing pregnancy, miscarriage, pregnancy and perinatal complication, birth weight, neonatal complication, and other adverse events.

Conception is defined with the result of serum β-hCG ≥10 mIU/ml measured 2 weeks after embryo transfer.

Clinical pregnancy is defined as detection of a gestational sac in the uterine cavity by a transvaginal ultrasound scan 20 days after conception confirmation.

An ectopic pregnancy is defined as a complication of pregnancy in which the embryo implants at any site other than the endometrial lining of the uterine cavity.

Ongoing pregnancy is defined as detection of a viable fetus with fetal heartbeat at 11–12 weeks of gestation.

Miscarriage is defined as pregnancies that eventuate in a spontaneous abortion before 20 weeks of gestation.

A live birth is defined as the delivery of any number of newborns at ≥ 28 weeks of gestation with heartbeat and breath.

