### Data analysis plan

The data will be analyzed by SPSS 16.0 (SPSS Inc., Chicago, IL, USA). The analysis will be conducted using intention-to-treat principles. The primary outcome, the live birth rate, will be compared between two groups using the Pearson chi-square test; secondary outcome parameters, such as the pregnancy rate, OHSS rate, and other rates, will be analyzed using the Pearson chi-square test. A per-protocol analysis will be performed according to the actual participants completing the entire trial. Continuous data are expressed as mean ± standard deviation, with Student’s test for data with normal distribution and Wilcoxon rank-sum test for nonnormal distribution. Categorical data are represented as frequency and percentage with chi-square analysis or Fisher’s exact test for expected frequencies less than 5. *P* < 0.05 will be considered significant.

The reasons for missing data will be recorded, and according to these reasons, four approaches may be considered: complete-case analysis, single imputation methods, estimating-equation methods, and methods based on a statistical model.

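### The 10% dropout inflation does not match the intention-to-treat analysis: at 836 women and the plan's own 10% dropout, power is about 76–78% unless dropouts are excluded or do not dilute the effect

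*Protocol article*

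**What the plan says.** All references are to the protocol article.

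- **Sample size.** The control rate comes from the group's own clinic: "Based on the retrospective data from our IVF clinic, the live birth rate of obese or overweight women is about 35" per cent. The target is 45% on orlistat, "at a significance level of 0.05 with a statistical power of 80" per cent. The result is then inflated: "The minimal sample size calculated is 752, and 836 participants will be enrolled in consideration of a dropout rate of 10" per cent.
- **Outcome and outcome assessments.** "The primary outcome is live birth after first fresh embryo transfer".
- **Data analysis plan.** "The analysis will be conducted using intention-to-treat principles". The test is fixed: "The primary outcome, the live birth rate, will be compared between two groups using the Pearson chi-square test". A per-protocol analysis of women who complete the trial is added. Four approaches to missing data are left open, one of them complete-case analysis.
- **Data collection and management.** Women who quit are asked whether they will still complete the scheduled follow-up.
- **Interventions.** Women are randomised after consent at screening and take study medication for 1–3 months before ovarian stimulation, up to the day of fresh transfer.

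**The concern.** Dividing a sample size by one minus the dropout rate compensates for women who disappear from the denominator. It does not compensate for women who stay in the denominator and carry a smaller treatment effect, or none.

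The inflation therefore belongs to an analysis of completers, while the main comparison is by intention to treat. A woman who leaves before stimulation and never has a fresh transfer cannot have the primary event. Her outcome is known rather than missing, and under intention to treat she counts as no live birth. A woman who stops medication but is followed through her cycle contributes an outcome, possibly at the control rate. In either case the contrast is narrower than 10 points.

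What is at stake is how the result is read. A null finding from a trial described as having 80% power for a 10-point gain would look somewhat more conclusive than the intention-to-treat comparison warrants.

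**Working it through.** **Inputs from the Sample size section:** control rate 0.35, orlistat rate 0.45, significance level 0.05, power 80%, dropout 10%. Allocation is 1:1 (Randomization and blinding). Sidedness is not stated. Two-sided is inferred from the Pearson chi-square test and because it reproduces the plan's figure.

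**Step 1: reproduce the plan.** Pooled-variance formula without continuity correction, with p̄ the mean of the two rates:

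n per arm = [1.960·√(2p̄(1−p̄)) + 0.842·√(p₁(1−p₁)+p₂(1−p₂))]² / (p₂−p₁)²

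With p̄ = 0.40 the square roots are 0.6928 and 0.6892, so n = 375.6, rounded up to 376 per arm, or 752. Then 752/0.9 = 835.6, rounded up to 836. Both stated figures reproduce exactly. Neither a one-sided test (592) nor a continuity correction (792) returns 752.

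**Step 2: power with all 836 analysed (418 per arm).**

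Power = Φ{ [√n·(p₂−p₁) − 1.960·√(2p̄(1−p̄))] / √(p₁(1−p₁)+p₂(1−p₂)) }

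*Dropouts count as no live birth in both arms.* The rates become 0.35 × 0.9 = 0.315 and 0.45 × 0.9 = 0.405, a difference of 9 points. Power = Φ[(1.8401 − 1.960 × 0.6788)/0.6758] = Φ(0.754) = 77.5%.

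*Orlistat-arm dropouts have the control rate.* The rates are 0.35 and 0.9 × 0.45 + 0.1 × 0.35 = 0.44, again a difference of 9 points. Power = Φ[(1.8401 − 1.960 × 0.6913)/0.6884] = Φ(0.705) = 75.9%, about 76%.

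**Step 3: when 80% is kept.**

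| How the 10% are handled | Women per arm | Rates | Power |
|---|---|---|---|
| Excluded (complete-case) | 376 | 35% vs 45% | 80.0% |
| All outcomes obtained, no dilution | 418 | 35% vs 45% | 84.0% |
| Counted as no live birth | 418 | 31.5% vs 40.5% | 77.5% |
| Orlistat-arm dropouts at control rate | 418 | 35% vs 44% | 75.9% |

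If only part of the dropout turns into non-events, power at 836 is 80.9% for 5% and 80.2% for 6% (32.9% vs 42.3%). For 7% it is 79.5%. The break-even is therefore a little above 6%.

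**Step 4: total needed for 80% in the two diluted cases.** The same formula gives 892 women for 31.5% vs 40.5% and 924 for 35% vs 44%. These figures show the size of the gap and are not a proposal to enrol more.

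**The case against.** The strongest reply is that the document does not say how dropouts are counted. Complete-case analysis is among the permitted approaches and gives 80.0%. Follow-up of women who quit is sought, and if it were complete and undiluted, power would be 84.0%. A woman who quits the trial may still have her transfer and a live birth, so the 10% need not all be non-events. This stands, and it is why the point is conditional. It does not remove the mismatch. Complete-case handling suits outcomes that are truly missing, not women who are known never to have reached transfer. Complete follow-up restores power only if women who stop treatment keep the full benefit; at the control rate, power is about 76%.

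A second reply is that the target, "We aim to test a difference of 10% in the live birth rate between treatment groups (45% in the orlistat group"), may already be an intention-to-treat difference. That is possible. But if the rates already allowed for dropout and outcomes were known for everyone, 752 would be enough. Adding 84 women (836 − 752) implies that the 10% were expected to leave the analysis.

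A third reply is that the loss is small, 2.5 to 4 points, around a control rate given only as approximate. That is correct and limits the weight of the point.

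A reader might infer a much larger loss from women who never have a fresh transfer. If the 35% were a per-transfer rate, and a further 10%, 20% or 30% of women had no fresh transfer on top of 10% dropout counted as non-events, power would be 70.7%, 63.3% or 55.5%. The document supports neither assumption. It says "the live birth rate of obese or overweight women is about 35" per cent without giving a base, and it gives no share of women without a fresh transfer. If the 35% is per woman starting treatment, cancelled cycles and cycles without fresh transfer are already in it.

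**Conclusion.** The point holds in a limited form. A reader might conclude that the sample size was miscalculated or that the design cannot reach 80% power. The documents support neither: both stated figures reproduce, and some permitted ways of handling dropouts keep 80% or more.

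What holds is that the inflation matches a completers' analysis while the main analysis is intention to treat, and the two sections are not reconciled. With all 836 analysed at the plan's own 10% dropout, power is about 76–78%. This rests on a two-sided test, on 35% and 45% being the rates among women who stay in the trial, and on the full 10% either having no live birth or, in the orlistat arm, having the control rate.

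**What to change.** Keep 836 and revise the wording of the Sample size section:

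1. Say that 80% power applies to 752 completers at 35% versus 45%.
2. Give the power of the intention-to-treat comparison of all 836 as about 76–78% at 10% dropout, and name the two assumptions behind that range.
3. Express both rates per randomised woman, which requires stating the base of the 35%.
4. If a loss through women without a fresh transfer is shown, present it as a sensitivity table labelled as resting on an assumed share.

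No extra participants and no change to the analysis are needed. The downside is a slightly less favourable stated power. Enrolment was still under way at submission, so the restatement could be made before results are known.

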### Screening

At the screening visit, patients who have been using orlistat or other weight-reducing aid/drugs will be excluded, and the couples sign the written informed consent after safety assessment, which includes fasting blood glucose, insulin, triglyceride (TG), total cholesterol (TC), high density lipoprotein (HDL), low density lipoprotein (LDL), lipoprotein a (Lp (a)), liver function, renal function, complete blood count (CBC), coagulation test, hepatitis B virus (HBV), hepatitis C virus (HCV), human immunodeficiency virus (HIV), syphilis, and routine urine. The standardized case report forms are completed to collect current medication status and previous medical history. A physical examination (height, body weight, waistline, hipline, blood pressure) and transvaginal ultrasound scan are performed. The basal sex hormones are tested in the local laboratories of the study sites. A diagnostic hysteroscopy is performed in patients who are suspected to have an abnormal uterine cavity after ultrasound scan. All participants are prescribed multivitamins and advised to have a healthy lifestyle, more physical activity, and a reduced-calorie, low-fat diet, and to avoid gaining weight rapidly during pregnancy. A schedule of enrollment, interventions, and assessment is provided in the Standard Protocol Items: Recommendations for Interventional Trials (SPIRIT) figure (Fig. 1). The flow chart of this study is shown in Fig. 2. The SPIRIT checklist is presented in Additional file 1.

**Fig. 1 Fig1:**
[figure not shown]
SPIRIT diagram for schedule of enrollment, interventions, and assessments. Safety assessment includes fasting blood glucose, insulin, TG, TC, HDL, LDL, Lp (a), liver function, renal function, CBC, coagulation test, HBV, HCV, HIV, syphilis, and routine urine. t1, 1–3 months after allocation; t2, day of ET; t3, 2 weeks after ET; t4, 5 weeks after ET; t5, 10 weeks after ET; t6, 28 weeks of gestation; t7, 37 weeks of gestation; t8, delivery; t9, 6 weeks after delivery

**Fig. 2 Fig2:**
[figure not shown]
Flow chart of subjects

### Randomization and blinding

A total of 836 patients will be enrolled, and a computer-generated random list generated by SPSS 16.0 (SPSS Inc., Chicago, IL, USA) will be used for randomization. The packaging is marked according to the random number list; the packaging and tablets of orlistat (Huadong Pharmaceutical Co., Ltd) and the placebo have the same appearance, which cannot be distinguished. The placebo is manufactured by Huadong Pharmaceutical Co., Ltd, and, in addition to the active ingredients, the rest of the excipient and the appearance and odor are exactly the same as orlistat. The random number list is kept strictly confidential by the Data Coordination Committee (DCC) staff, and the researchers who are in charge of the enrollment have no access to the list. Study personnel are blinded to upcoming treatment group allocation. Participants will receive the medication (orlistat or placebo with a 1:1 ratio). The appearance of orlistat and placebo is identical in packaging, and the participants and all research staff do not know the allocation until the end of the study. The quality of the placebo, such as contents and bacteria contaminations, was controlled rigorously according to the GMP standard.

### Interventions

Participants are randomized to receive either orlistat 120 mg p.o. three times daily (intervention) or placebo 120 mg p.o. three times daily after signing consent at the screening visit. Both groups of participants will take orlistat or placebo for 1–3 months before ovarian stimulation and to the day of fresh embryo transfer.

The protocol of ovarian stimulation is decided by the physicians according to the patients’ characteristics. Oocyte retrieval is performed 34–36 h after human chorionic gonadotrophin (hCG) injection by experienced physicians, and oocytes are inseminated by IVF or ICSI according to the quality of sperm. On day 3 or 5 of the embryo culture, the quality of embryos is assessed by experienced embryologists, and the morphological criteria are selected by the local laboratory. No more than three embryos on day 3 or 5 will be transferred, and the rest of the embryos will be frozen according to local experience. The protocol of luteal phase support and the day of starting will be determined by the local center. The serum hCG test is performed after 2 weeks of transfer, and if the test is positive, follow-up will be continued to the end of pregnancy or delivery.

### Outcome and outcome assessments

The primary outcome is live birth after first fresh embryo transfer. The secondary outcomes include changes of body weight, moderate and severe ovarian hyperstimulation syndrome (OHSS), dose of gonadotrophin during ovarian stimulation, numbers of oocytes, embryos of high quality, conception, clinical pregnancy, ongoing pregnancy, miscarriage, pregnancy and perinatal complication, birth weight, neonatal complication, and other adverse events.

Conception is defined with the result of serum β-hCG ≥10 mIU/ml measured 2 weeks after embryo transfer.

Clinical pregnancy is defined as detection of a gestational sac in the uterine cavity by a transvaginal ultrasound scan 20 days after conception confirmation.

An ectopic pregnancy is defined as a complication of pregnancy in which the embryo implants at any site other than the endometrial lining of the uterine cavity.

Ongoing pregnancy is defined as detection of a viable fetus with fetal heartbeat at 11–12 weeks of gestation.

Miscarriage is defined as pregnancies that eventuate in a spontaneous abortion before 20 weeks of gestation.

A live birth is defined as the delivery of any number of newborns at ≥ 28 weeks of gestation with heartbeat and breath.

### Safety assessment

Adverse events (AEs) are any untoward medical occurrences associated with the subject’s participation in the research, which do not necessarily have a causal relationship with the study intervention. Serious adverse events (SAEs) are events that occur during the subject’s participation in research that meet any of the following criteria: death, life-threatening, severe or persistent disability, requiring inpatient hospitalization or prolongation of existing hospitalization, neonatal death up to 6 weeks after delivery, congenital anomaly or birth defect, or any events deemed serious by the local principal investigator.

Participants will be questioned to report all AEs and unintended concomitants medications at each visit, and all reported AEs will be assessed and recorded. All abnormal changes of blood tests will be evaluated by the investigators. SAEs will be reported in 5 days; SAEs which are unintended and possibly associated with interventions will be reported within 24 h.

### Data collection and management

To ensure the accuracy of outcome assessments and data collection, all of the physicians, nurses, and research assistants will attend a training workshop before the start of the trial. All attenders will be provided with a protocol and standard operation procedures, and will discuss the topics they may feel confused about until everyone is totally clear about the procedures. The DCC is responsible for the monitoring tasks of the trial. Personnel of Shandong University will regularly check the data from different sites, determine the issues that affect the quality and speed of research, and take corresponding measures.

After screening and signing of informed consent, the current medication status, previous medical history, height, body weight, waistline, hipline, blood pressure, transvaginal ultrasound scan, and basal sex hormones will be recorded.

OHSS, dose of gonadotrophin, and information on oocytes and embryos will be assessed from the start of ovarian stimulation to the day of the pregnancy test.

Serum β-hCG will be measured 2 weeks after embryo transfer. If the serum β-hCG test is positive, a transvaginal ultrasound scan will be performed 20 days later to detect the gestational sac.

During pregnancy beyond 12 weeks, participants are contacted by telephone call at 28 and 32 weeks to inquire about pregnancy complications, AEs, and combination therapy.

At delivery, obstetrical and perinatal complications and neonatal information are obtained with reference to obstetric medical records and neonatal medical records.

At 6 weeks after delivery, postpartum complications and neonatal complications are followed up by telephone call.

Data are collected and recorded on a standard case report form, and when the visit is completed in every site, all of the recorded data will be entered into the web-based data system by the double-entry method.

Any participant may quit the trial at any time for any reason. If any patients want to quit, clinicians will ask whether they agree to finish the follow-up according to the trial schedule. All patients who quit and are lost to follow-up will be recorded.

